## Abstract

Despite the increasing number of older people, many with cognitive impairment (CI), in hospitals, there is yet to be an evaluation of hospital-wide interventions improving the management of those with CI. In hospitalized patients with CI, there are likely to be associations between increased complications that impact on outcomes, length of stay, and costs. This prospective study will evaluate the effectiveness of an established hospital CI support program on patient outcomes, patient quality of life, staff awareness of CI, and carer satisfaction. Using a stepped-wedge, continuous-recruitment method, the pre-intervention patient data will provide the control data for usual hospital care. The intervention, the Dementia Care in Hospitals Program, provides hospital-wide CI awareness and support education, and screening for all patients aged 65+, along with a bedside alert, the Cognitive Impairment Identifier. The primary outcome is a reduction in hospital-acquired complications: urinary tract infections, pressure injuries, pneumonia and delirium. Secondary outcome measures include cost effectiveness, patient quality of life, carer satisfaction, staff awareness of CI, and staff perceived impact of care. This large-sample study across four sites offers an opportunity for research evaluation of health service functioning at a whole-of-hospital level, which is important for sustainable change in hospital practice.

## 1. Introduction

Dementia is the leading cause of disability burden and the second leading cause of burden of disease for people aged 65+ [1]. Eighty-three-thousand patients with dementia are admitted to hospital each year in Australia [1].

People with dementia experience poorer outcomes of hospitalization, including higher rates of hospital-acquired complications [2]; higher rates of discharge to residential care [3]; higher morbidity [4]; and more bed days in hospital [5]. Outcome measurement is hampered by difficulty in relying on documentation of dementia diagnosis as it often goes undetected and, if detected, often goes undocumented [6].

In complex hospital environments, the diagnosis and documentation of dementia is made difficult by the presence of other causes of memory and thinking disorders, such as delirium, head injury, or narcosis. These disorders can be symptomatically similar to dementia regarding presentation of confusion and disorientation. The higher risks of hospital-acquired complications documented in people with dementia [2] could also be associated with these “failures in cognition”. Consequently, the term ‘cognitive impairment’ (CI) can be used to describe the memory and thinking difficulties seen in hospital without ascribing a diagnosis. CI is increasingly used as a term to encompass the breadth of disorders causing brain dysfunction, and in hospitals is most likely caused by dementia, delirium or stroke [7].

Adults admitted to Australian hospitals are assumed to have the cognitive capability to respond to the demands of hospital care, which require information retention, dexterity, insight and empathy. Some hospital safety systems, such as medication safety, rely on this cognitive ability in order to be effective [8]. It is estimated, however, that 30% of patients aged 65+ have CI during their hospital stay [7]. While dementia is the focus of much of the current research related to risks of hospitalization, this study will target patients with CI, who are likely to share similar high levels of risk.

Risk of hospitalization for patients with CI is compounded by the complexity of the hospital environment. Hospital staff are known to be inadequately equipped to identify, or respond appropriately to, people with dementia or other cognitive impairments [7]. Staff report difficulty in engaging with patients with CI and their families [9], and that older people’s needs may not align well with the acute hospital setting [10]. Patients with CI require higher support needs for communication, procedural interventions, ambulation, toileting, and medication administration [11]. Positive nursing work environments with manageable workloads [12,13,14], and acute models for the care of older people, have been associated with lower rates of hospital-acquired complications [15,16], indicating that, with suitable models of care, these are potentially modifiable patient outcomes.

Risk screening combined with appropriate mitigation processes on admission to hospital is a well-recognized approach to identify and reduce patient risk [17]. Similarly, screening for CI provides an opportunity for follow-up interventions and the implementation of appropriate care. Following up an effective screening program with a process for hospital-wide awareness of patients with CI, embedded by way of a simple staff–patient communication strategy, has the potential to reduce incidence of complications, improve hospital outcomes, reduce length of stay, and lower costs.

The Dementia Care in Hospitals Program (DCHP) provides an intervention that aims to change the hospital care paradigm from one where all hospitalized adults are expected to manage the complex demands of hospital care, to one where it is recognized that additional support and a change to the hospital processes and environment are needed for those with CI.

The DCHP is a hospital-based education and system-change program linked to screening for CI. Unlike dementia diagnosis, screening for CI does not require complex algorithms: it is a functional descriptor of impairment of memory and thinking associated with risk. Analogous to falls, the identification of this sort of functional risk can be embraced by nursing and allied health staff.

Previous evaluation of the program showed improvements in staff knowledge, confidence and comfort in dealing with patients with CI [9], and increased carer satisfaction [18]. The effect of the program on clinical outcomes, patient quality of life, and cost effectiveness has, however, not yet been measured.

### Study Aim and Hypotheses

The primary aim of this hospital-based interventional study is to determine if the DCHP will reduce hospital-acquired complications in people aged 65+ with CI, compared to those receiving usual hospital care. Secondary aims include an economic evaluation of the intervention compared to usual hospital care, and an examination of its impact on patient quality of life, carer satisfaction, staff awareness of CI, and staff perceived burden of care when caring for patients with CI in hospital.

## 2. Materials and Methods

### 2.1. Study Design and Setting

The impact evaluation of the DCHP will use a prospective, stepped-wedge, cross-sectional, continuous-recruitment study design. Patients aged 65+ will be screened for CI within 24 h of hospital admission and included if they have CI. Recruitment will occur continuously over the study period, with individual patients remaining in the study for the length of their hospital stay. Patients aged 65+ admitted to the target wards of a single hospital are referred to as a cluster; there will be four clusters across four Australian jurisdictions. Three sites are large metropolitan hospitals with a university affiliation; and one is a regional hospital. At each hospital, the wards selected to implement the DCHP will be determined by level of interest from the nursing leadership team and a requirement for a spread of wards across medical, surgical, and acute aged care. The Baseline period was determined by the estimated time required to achieve 80% patient screening and 40% staff education. The 42-week intervention period was considered sufficient time for change to be measurable within the constraints of the project funding. Consistent with a stepped-wedge trial design [19], each cluster provides both before and after observations, and clusters incrementally shift from control to intervention (see Table 1—Stepped-Wedge Timeline). Hospital-acquired complications data will be analyzed cross-sectionally.

### 2.2. Study Population

The participant pool will comprise all patients aged 65+ (50+ for those identifying as Aboriginal and Torres Strait Islander) admitted for more than 24 h to participating wards and screened for CI using a validated screening tool. There will be no patient exclusions. Patients transferred between participating wards will be counted once. Patients transferred to a participating ward from a nonparticipating ward will be included if they stay on the participating ward for longer than 24 h, and patients transferred from a participating ward on which they had stayed for greater than 24 h to a nonparticipating ward will also be included. Consent was confirmed with each participating health service via waiver of consent documentation.

The Dementia Quality of Life Measure (DemQol) and Carer surveys will be completed by a subset of the participant pool who screen positive for CI, and their carers. Staff surveys will be completed by personnel on the relevant wards who have regular contact with the target patient group. These will include clinical (nursing, medical and allied health) and nonclinical staff (ward clerks, food and domestic staff, porters and cleaners) on the participating wards.

### 2.3. Materials

The choice of screening tool was determined by the hospitals at the time of site selection. It was requested that a validated screening tool be used, and hospitals chose tools that were already embedded in current practice. Criteria and screening tools for CI and study inclusion are presented in Table 2.

Each hospital will receive face-to-face and remote support from the DCHP National Implementation Team based at Ballarat Health Services. Project implementation will support a full-time on-site project officer, materials, and travel funding. The implementation team will visit each site for a project launch and education session. Local education will be supported by the project officer and provision of an education package that is appropriate for both clinical and nonclinical staff.

### 2.4. Data

Hospital-acquired complication data will be drawn from routinely collected hospital data sets and submitted to the Health Roundtable (HRT) [24], which is a not-for-profit membership organization of participating hospitals across Australia and New Zealand. HRT holds routinely collected data for 8 years for all the hospitals in the DCHP. The hospital-acquired complications for the evaluation were derived from hospital-coded patient records. This method is based on work by Needleman et al. [12], and updated to ICD10 by Bail et al. [2]. All the diagnostic codes for the patients’ episodes will be examined separately. Patients with at least one of four complications will be recorded as positive for a hospital-acquired complication.

Staff surveys, carer surveys and patient DemQoLs [25,26] will be collected during the pre-intervention period and at approximately six months post-intervention.

Ethics approval has been obtained for data sharing with the external evaluation team. Patient data, which will be de-identified prior to analysis, will include patient descriptors (e.g., age, name, Unit Record Number (UR), Aboriginal and Torres Strait Islander (ATSI) status, comorbidity index), and episode descriptors (e.g., length of stay, discharge ward).

Data will be stored on a secure server with restricted access. Data will be entered into Excel spreadsheets on-site and at the DCHP National Office for later analysis using the SPSS and Stata statistical software packages. To ensure data integrity, all data cleaning and data entry will be completed by two research assistants using a cross-check methodology. Responsibility for appropriate and secure data storage rests with the primary investigator and the evaluation team.

### 2.5. Outcome Measures

The primary outcome measure will be the change in the rate of the combined risk of one or more of the following hospital-acquired complications: urinary tract infection, pressure injury, pneumonia or delirium before and after the adoption of the DCHP. The rate of this combined risk will be determined for patients who screen positive for CI over a 12-week period before the introduction of the DCHP, and for patients who screen positive for CI over four consecutive 12-week periods during implementation. A summary of primary and secondary outcomes as well as relevant instruments and sources is provided in Table 3. Falls rates will be a secondary outcome as per Medibank Private methodology, using the Y9222 flag within the ICD code to indicate whether a fall occurred in hospital or not [27].

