#### 2.6.5. Sample Size, Power Calculation and Analysis

Based on a conservative estimate of 750 positive screens for CI in each period, the target sample size is a total of 3750 patients. The required sample has been calculated with power 0.8, type I error 0.05 and design effects based on clustering effect (ICC) at site (0.05) level. It is estimated that for a complication rate ranging from 20–26%, this sample size will enable detection of a 22–25.5% or more reduction in risk ratio (RR). This is equivalent to a minimum 5–5.5% reduction in absolute risk. A generalized linear mixed model for a binary outcome with time epoch as a fixed factor and hospitals as a random effect for an incomplete stepped-wedge design with a cross-sectional design was adopted for the power calculation [29]. Stata software was used for this purpose [30].

In relation to the secondary outcomes, based on type I error of 0.05 and a power of 0.9, a target sample size of 160 DemQols per site (80 at baseline and 80 at intervention) is required to detect 15-point differences in health-related quality-of-life score.

Assuming a type I error of 0.05 and a power of 0.8, a target sample size of 140 carer surveys (70 at baseline and 70 at intervention) is required to detect a minimum effect size of 0.4.

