## 3. Discussion

A stepped-wedge design is a logical fit, given that hospitals are constantly changing their care models in different ways and across varying time courses. The stepped-wedge methodology is designed to control for potential bias that occurs as a result of variations in hospital practice and the introduction of new regulations. In addition, while the value of the program has been accepted by the funding body and participating sites on the basis of previous rollouts and grey literature reports [9,18], this study is expected to provide a platform for adoption of the DCHP across each State in Australia. Such an outcome requires robust evidence of clinical benefit and cost effectiveness, particularly as Australia is a federated democracy where acute hospital care is the responsibility of individual States.

The order of implementation is not randomized. While randomization would be preferable, with only four sites this is not critical. In addition, introducing significant change in hospitals requires hospital ownership of the program, which is facilitated by a negotiated start date reflecting organizational readiness.

This evaluation will measure the hospital-acquired complication rate in a large prospective cohort of older Australian hospital patients with and without CI. The international literature on hospital-acquired complication rates in patients with dementia has been based on retrospective data [31], which is known to be incomplete and potentially missing half the at-risk group [3]. New international studies are prospective but smaller in terms of sample sizes [32]. Real-time capture of data on all older patients with CI in hospital may have the effect of either decreasing or increasing the recorded hospital-acquired complication rate. We hypothesize that patients with mild symptoms, who are possibly missed in retrospective studies, are at greater risk because they receive no or little support beyond that given for their documented comorbidities. Therefore the risk rate will be higher. It is possible that this assumption is incorrect and the complications are rather a reflection of the degree of CI, resulting in a reduced complication rate reflecting milder CI.

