## Figures and Tables

**Figure 1 ijerph-15-01878-f001:**
[figure not shown]
Cognitive Impairment Identifier (CII).

**Table 1 ijerph-15-01878-t001:** Stepped-Wedge Timeline.

Timeline	February 2014 to February 2015	March 2015	June 2015	September 2015	December 2015	March 2016	May 2016	July 2016	September 2016	December 2016	February 2017
Weeks	52	12	12	12	12	12	12	12	12	12	12
1	BL1 Normal Practice	BL1 Normal Practice	**BL2 Training**	**BL2 Training**	T1	T2	T3	T4			T5
2	BL1 Normal Practice	BL1 Normal Practice	BL1 Normal Practice	**BL2 Training**	**BL2 Training**	T1	T2	T3	T4		T5
3	BL1 Normal Practice	BL1 Normal Practice	BL1 Normal Practice	BL1 Normal Practice	BL1 Normal Practice	**BL2 Training**	T1	T2	T3	T4	T5
4	BL1 Normal Practice	BL1 Normal Practice	BL1 Normal Practice	BL1 Normal Practice	BL1 Normal Practice	BL1 Normal Practice	**BL2 Training**	T1	T2	T3	T4

BL1 = Normal Practice; BL2 = Baseline / Training Phase (yellow); T1–T5 = Intervention phases (green).

**Table 2 ijerph-15-01878-t002:** Cognitive Impairment Screening Tools.

Tool	Abbreviation	Criteria for Positive CI Screen	Used by Site	Reference
Abbreviated Mental Test	AMT	Score≤ 7	1	Hodkinson [20]
Mini-Cog		Recall 1 or 2 of 3 items and abnormal Clock Drawing; or recall of 0 of 3 words.	4	Borson [21]
Abbreviated Mental Test Score 4 *	AMT4	Score of 3 or less	2 and 3	Swain [22]
Clock Drawing Test ^	CDT	Not all clock numbers present, spaced unevenly, or hands pointing to incorrect time.	2, 3 and 4	Scanlan [23]

* Only used in conjunction with Clock Drawing Test (CDT); ^ used in conjunction with either AMT4 or MiniCog.

**Table 3 ijerph-15-01878-t003:** Outcome measure, instruments and data sources.

	Outcome Measure	Instrument/Source
**Primary Outcome: Clinical**	The change in the rate of the combined risk of one or more of the hospital-acquired complications: urinary tract infection, pressure injury, pneumonia and delirium, before and after the adoption of the DCHP.	Health Roundtable [24]
**Primary Outcome: Cost**	Difference in mean total cost of hospitalization for patients aged 65+ before and after the adoption of the DCHP. Difference in mean total cost of hospitalization for patients aged 65+ who screen positive for CI before and after the adoption of the DCHP.	Health Roundtable [24]
**Secondary Outcome: Cost Effectiveness**	Quality of life Length of stay Cost effectiveness	DemQol ^ [25,26] Health Roundtable [24]

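### The primary outcome is a before/after change over windows counted from each hospital's own start, and the power model's time epoch is undefined: one reading confounds the effect with calendar time, the other leaves about 55% power

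*Protocol article*

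**What the plan says.** Section 2.5 frames the primary outcome as a change in the combined complication rate before versus after adoption. The rate is taken in patients with a positive CI screen, in these windows: "over a 12-week period before the introduction of the DCHP, and for patients who screen positive for CI over four consecutive 12-week periods during implementation". Table 3 repeats the before/after wording for the primary outcome and uses it for cost: "Difference in mean total cost of hospitalization for patients aged 65+ before and after the adoption of the DCHP".

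Section 2.6.5 gives the size: "Based on a conservative estimate of 750 positive screens for CI in each period, the target sample size is a total of 3750 patients". It states power 0.8, type I error 0.05, a site-level ICC of 0.05, and a detectable reduction of 5-5.5 percentage points (22-25.5% relative) for rates of 20-26%. The power model is a generalized linear mixed model "with time epoch as a fixed factor and hospitals as a random effect". The same sentence goes on to call the design an incomplete, cross-sectional stepped wedge. The article does not say whether an epoch is a calendar column of Table 1 or a window counted from a hospital's start.

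The Discussion states the intent: "The stepped-wedge methodology is designed to control for potential bias that occurs as a result of variations in hospital practice", and it includes new regulations in this. The Limitations section likewise expects the study design to absorb the gradual uptake of national guidance on CI screening and delirium.

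**The concern.** A stepped wedge separates a programme effect from shared calendar change only when hospitals that have crossed over are compared with hospitals that have not, at the same calendar time. In a model this means a calendar-time term beside the programme term. The outcome as written does not contain one: its windows move with each hospital's start, so every hospital's after lies later in calendar time than its before, and pooling the hospitals cannot cancel a shared trend.

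The risk is concrete here. Delirium is one of the four components, outcomes come from routinely coded records, the article itself expects national guidance to be taken up during the study, and the order of starts is negotiated rather than randomized. What is at stake is either whether the primary result can be attributed to the programme or whether the stated power is right, depending on what time epoch means.

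**Working it through.** **Inputs from the protocol article.** Four hospitals (section 2.1); one window before and four after (2.5); 750 patients per period, 3750 in total, ICC 0.05, power 0.8, alpha 0.05, rates 20-26%, detectable 5-5.5 points (2.6.5); the stagger in Table 1.

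**Assumptions.** Equal spread, 750/4 = 187.5 patients per hospital-period; the last BL2 column as the before window; two-sided alpha; outcome variance taken at the mean of the control and reduced rates, except where stated.

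**1. Layout.** 5 x 750 = 3750 reproduces the total. In Table 1 the last BL2 column plus T1-T4 runs from September 2015 for hospital 1 to February 2017 for hospital 4. That is 20 hospital-periods over eight calendar columns, holding 1, 2, 3, 4, 4, 3, 2 and 1 hospitals, or about 188 to 750 patients each. The five periods of 750 are therefore the windows counted from each start, not five calendar columns.

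**2. Epoch = window counted from start.** The fixed part has an intercept, the programme indicator and four epoch indicators (T1-T4), so 6 columns. The programme indicator equals T1 + T2 + T3 + T4, so the rank is 5 of 6. The programme effect cannot be estimated beside the epoch factor. What remains is the before/after contrast, without calendar adjustment.

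A shared linear drift of 1 point per column then enters that contrast as (1 + 2 + 3 + 4)/4 = 2.5 points. A drift of 5/2.5 = 2.0 to 5.5/2.5 = 2.2 points per column would mimic the whole stated effect.

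**3. Epoch = calendar column.** The fixed part has an intercept, the programme indicator and seven column indicators, so 9 columns. The rank is 9 of 9, and the bias from the same drift is zero.

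**4. Standard errors.** Before/after: SE = sqrt[(1 - ICC) x p(1 - p) x (1/750 + 1/3000)], with p the mean rate.
- 20% falling by 5 points: p = 0.175; SE = sqrt(0.95 x 0.1444 x 0.001667) = 0.0151.
- 26% falling by 5.5 points: p = 0.2325; SE = sqrt(0.95 x 0.1784 x 0.001667) = 0.0168.

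Adding calendar columns (generalized least squares on the 20 cells with a random hospital intercept) multiplies these by 1.56, to 0.0236 and 0.0263.

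**5. Power and detectable difference.** Power = Phi(d/SE - 1.96); the detectable difference solves d = (1.96 + 0.84) x SE.

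| | Before/after | Calendar columns |
|---|---|---|
| Power, 5 points from 20% | 0.91 | 0.56 |
| Power, 5.5 points from 26% | 0.91 | 0.55 |
| Detectable from 20% | 4.3 points | 6.5 points (33% relative) |
| Detectable from 26% | 4.7 points | 7.3 points (28% relative) |

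The relative figures in 2.6.5 give 25.5% x 20% = 5.1 and 22% x 26% = 5.72 points; calendar-adjusted power for these is 0.58 and 0.59. Reaching 80% would take about 6,200-6,800 patients. The plan's own 5-5.5 points at 80% is reproduced by neither model: it lies between them.

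**6. Sensitivity, total held at 3750.** Other ways of including BL1, BL2 and T5 columns with calendar adjustment gave two-sided detectable differences of 6.55 points or more at 20% and 7.32 or more at 26%. An idealised complete 4 x 5 wedge gave 6.1 and 6.8. One-sided testing on the 20 cells gave 5.8 and 6.5.

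**7. Illustration of unadjusted bias.** Suppose no programme effect and a shared fall of delta between the before window and the mean of T1-T4. The two-sided rejection rate is Phi(delta/SE - 1.96) + Phi(-delta/SE - 1.96), with SE at the base rate (0.0159 at 20%, 0.0175 at 26%). For delta = 1, 2 and 3 points this gives 10%, 24% and 47% at 20%, and 9%, 21% and 40% at 26%. With simulation and slightly different variance conventions the ranges are about 9-10%, 20-24% and 39-48%. The plan gives no figure for drift, so these are assumed values.

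**The case against.** Section 2.5 says which patients are counted; it does not set the levels of a model factor. A total can be accumulated by window since start and still be modelled by calendar column. The description as an incomplete stepped wedge fits the 1, 2, 3, 4, 4, 3, 2, 1 pattern of Table 1, and a model with a programme term works only under the calendar reading. The mixed model is given for the power calculation alone, no primary analysis model is stated, and a statistical analysis plan not shown may supply one.

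Much of this stands. A reader might infer that the epochs are counted from each start and that the trial will therefore credit shared calendar change to the programme. The document does not support that: the term is undefined, and calendar epochs fit the text at least as well. Nor is it shown that hospitals still in baseline never act as concurrent controls; in December 2015, for example, hospital 2 is in BL2 while hospital 1 is in T1. The error rates in step 7 apply only to a contrast without calendar adjustment.

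Two things survive. The article does fix the outcome wording and the sample size, so these are not matters left to a later plan. And the calendar reading, which rescues identification, does not rescue the stated power.

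**Conclusion.** The point holds as a two-sided problem. If time epoch means the windows of section 2.5, the programme effect is aliased with it, and shared calendar change cannot be removed, contrary to the Discussion and Limitations. If it means the Table 1 columns, the effect is identified, but 3750 patients give about 55% power (0.55-0.59) for the stated reduction rather than 80%, with a detectable difference of about 6.5-7.3 points.

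The power figures rest on equal hospital-periods of 187.5, the last BL2 column as baseline, two-sided 0.05 and ICC 0.05. The stated 5-5.5 points does not reveal which reading was used. The cost outcomes share the before/after wording and so the same exposure, for instance to price change; no size is put on it, because the article gives neither cost variability nor an inflation rate.

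**What to change.** In sections 2.5 and 2.6.5 and in Table 3:

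- Define time epoch as the Table 1 calendar column.
- State the primary effect as the coefficient of a programme on/off indicator in a model with hospital and calendar-column terms.
- Label the raw rates by baseline and T1-T4 as descriptive.
- Analyse the cost outcomes with the same calendar adjustment.
- Restate the power, or the detectable difference, for 3750 patients under that model, naming which Table 1 columns count as control.

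This changes wording and one calculation and needs no new data. The price is a standard error about 1.6 times that of the unadjusted before/after contrast and a less favourable power statement. If 80% power for 5-5.5 points is to be kept, about 6,200-6,800 patients would be needed under the assumptions above.
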